### Power and sample size

We consider 14 points on PRWE to be the minimum clinical difference necessary to justify the additional costs of surgery compared to non-surgical treatment. This is the MCID determined by Sorensen [32] and larger than the 11.5-point estimate determined by Walenkamp [38].

A total of 128 patients (64 in each group) will provide 90% power to detect a difference of 14 points on the PRWE scale at a significance level of 0.05. We aim to recruit 160 patients to allow for 20% loss to follow-up. Two previous RCTs that had each published results at the time of our sample size calculation reported loss-to-follow-up rates of 19% [5, 39]. Given that this is a multi-centre trial, the closing date for recruitment (31 December 2018) was set based on expected recruitment of 160 randomised participants. However, by the time recruitment closed, 164 participants had been recruited.

The observational arm includes all eligible patients not consenting to randomisation. We recruited 136 participants to the observational arm to the trial.

### Statistical analysis

#### Analysis principles

Data will be analysed using statistical analysis package SAS (SAS Institute Inc., Cary, NC, USA) and R statistical computing software [40].

Recruitment for CROSSFIRE concluded in January 2019. The final analysis will commence after the 12-month data collection is complete. The de-identified data-set will be inspected for missing data and data quality.

Study outcomes produce both continuous and categorical data. Continuous data will be inspected for normality. Continuous data will be presented by mean values and standard deviations (SDs) as well as mean difference (MD) and 95% confidence interval (CIs) (see Tables 4 and 5 as examples) if normally distributed, otherwise by median and interquartile range.

**Table 4 Tab4:** Secondary outcomes at 3 months for the randomised group

Outcome		Randomised		
		Surgical (*n*=__)	Non-surgical (*n*=__)	MD (95%CI) or odds ratio (95%CI)
PRWE, mean (SD)				
ED-5D-5L, mean (SD)	EQ-UI			
	EQ-VAS			
Pain on NRS (0-10)				
Patient-reported treatment success n(%)	Very successful			
	Successful			
	Neutral			
	Unsuccessful			
	Very unsuccessful			
Therapy utilisation up to 3 months (Yes/No) n(%)				
Therapy utilisation at 3 months (Yes/No) n(%)				
Radiographic measures, mean (SD)	Dorsal angulation (degrees)			
	Radial tilt (degrees)			
	Ulnar variance (mms)			
	Articular step (mms)

**Table 5 Tab5:** Secondary outcomes at 3 months for the observational group

Outcome		Observational		
		Surgical (*n*=__)	Non-surgical (*n*=__)	MD (95%CI) or odds ratio (95%CI)
PRWE, mean (SD)				
ED-5D-5L, mean (SD)	EQ-UI			
	EQ-VAS			
Pain on NRS (0-10)				
Patient-reported treatment success n(%)	Very successful			
	Successful			
	Neutral			
	Unsuccessful			
	Very unsuccessful			
Therapy utilisation up to 3 months (Yes/No) n(%)				
Therapy utilisation at 3 months (Yes/No) n(%)				
Radiographic measures, mean (SD)	Dorsal angulation (degrees)			
	Radial tilt (degrees)			
	Ulnar variance (mms)			
	Articular step (mms)			

Categorical data will be summarised according to frequency (*n*) and incidence (%) (see Table 5). Comparison between treatment groups will be tested using chi-squared and odds ratio with 95% CI.

Comparisons between treatment groups will be tested at the two-sided, 5% significance level. *P* values will be reported to three decimal places if *P* > 0.001. *P* values < 0.001 will be reported as < 0.001. Means and SDs will be reported to one decimal place.

#### Data integrity

The study compares two treatments that comprise usual care. A Data Safety Monitoring Board (DSMB) was not required to be convened.

Interim analysis of data completeness and accuracy of data entry was conducted on two occasions during the data collection phase. The paper files from data collected by telephone were cross-checked against the electronic database. An audit of x-ray data was also be completed.

There are potential sources of bias. The types of bias and the efforts made to reduce their risk included:
Selection bias; randomisation occurs immediately after consent and immediately prior to treatment assignment using a central computer-based randomisation service by telephone, using stratification and minimisation to ensure balanced treatment allocation for site, age and genderPerformance bias; treatment, other than the interventions under study is identical in both groups. Participating surgeons have equipoise regarding the two treatment alternatives and were instructed not to express a treatment preference to the participants recruited to the randomised studyDetection bias; the primary outcome is collected from participants by blinded researchers, by telephone. The statistician and investigators will be blinded to the treatment group during the analysisAttrition bias; attempts are made to minimise missing data, such as obtaining multiple contact details at recruitment and using telephone follow up rather than mail. Interim analyses of data completeness and accuracy of data entry are conducted on two occasions in the data collection periodReporting bias; the de-identified participant-level dataset and statistical code will be made available for collaborative research projects. All pre-specified outcomes will be reported

### Methods for handling missing data

In the analysis, missing data will be dealt with according to the instructions on the use of the outcome tools (PRWE, DASH and EQ-5D-5L). The need to impute will be assessed and confirmed at the time of review of blind data. If greater than 10% of the primary outcome data is missing from the randomised sample, then missing primary outcome data will be imputed using multiple imputations based on baseline data including age, gender and fracture type as well as PRWE score at 3 months. A completed case analysis will be performed as a sensitivity analysis.

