### Primary analysis

The primary analysis will follow the intention-to-treat (ITT) principle. The primary outcome is the PRWE score at 12 months for the participants recruited to the randomised trial. The MD in PRWE scores between the surgical and non-surgical groups will be tested using a two-sample *t* test. The mean values, SDs, MDs and 95% CIs will be displayed (see Table 6 for example). The medians and inter-quartile ranges will be represented in a box plot (see Fig. 2 for example).

**Table 6 Tab6:** Primary and secondary outcomes at 12 months for the randomised group

Outcome		Randomised		
		Surgical (*n*=__)	Non-surgical (*n*=__)	Mean difference (95%CI)
PRWE				
DASH				
ED-5D-5D, mean (SD)	EQ-UI			
	EQ-VAS			
Pain on NRS (0-10)				
Patient-reported treatment success n(%)	Very successful			
	Successful			
	Neutral			
	Unsuccessful			
	Very unsuccessful			
Patient-reported bother with appearance n(%)	Not at all			
	Bothered a little			
	Bothered moderately			
	Very bothered			
	Extremely bothered			
Radiographic measures, mean (SD)	Dorsal angulation (degrees)			
	Radial tilt (degrees)			
	Ulnar variance (mms)			
	Articular step (mms)

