### Sensitivity analyses

In order to investigate the impact of missing data, a completed case analysis of the primary and secondary outcomes at 12 months will be performed and compared with the analysis using imputed data (if required); see Table 11 for example.

**Table 11 Tab11:** Sensitivity analysis. Primary and secondary outcomes at 12 months, based on completed cases analysis of randomised group

Outcome		Completed cases in randomised group		
		Surgical (*n*=__)	Non-surgical (*n*=__)	Mean difference (95%CI)
PRWE				
DASH				
ED-5D-5D, mean (SD)	EQ-UI			
	EQ-VAS			
Pain on NRS (0-10)				
Patient-reported treatment success n(%)	Very successful			
	Successful			
	Neutral			
	Unsuccessful			
	Very unsuccessful			
Patient-reported bother with appearance n(%)	Not at all			
	Bothered a little			
	Bothered moderately			
	Very bothered			
	Extremely bothered			
Radiographic measures, mean (SD)	Dorsal angulation (degrees)			
	Radial tilt (degrees)			
	Ulnar variance (mms)			
	Articular step (mms)			

In order to investigate the impact of non-compliance with the protocol, an as-treated analysis and a per-protocol analysis of the primary and secondary outcomes at 12 months will be performed and the results will be compared with the ITT analysis; see Tables 12 and 13 as examples. Non-operative treatment will be defined as a minimum of 28 days in the plaster splint for the purposes of the per-protocol analysis.

**Table 12 Tab12:** Sensitivity analysis. Primary and secondary outcomes at 12 months, based on as-treated analysis of randomised group

Outcome		As-treated allocation of randomised group		
		Surgical (*n*=__)	Non-surgical (*n*=__)	Mean difference (95%CI)
PRWE				
DASH				
ED-5D-5D, mean (SD)	EQ-UI			
	EQ-VAS			
Pain on NRS (0-10)				
Patient-reported treatment success n(%)	Very successful			
	Successful			
	Neutral			
	Unsuccessful			
	Very unsuccessful			
Patient-reported bother with appearance n(%)	Not at all			
	Bothered a little			
	Bothered moderately			
	Very bothered			
	Extremely bothered			
Radiographic measures, mean (SD)	Dorsal angulation (degrees)			
	Radial tilt (degrees)			
	Ulnar variance (mms)			
	Articular step (mms)

**Table 13 Tab13:** Sensitivity analysis. Primary and secondary outcomes at 12 months, based on per-protocol analysis of randomised group

Outcome		Per-protocol allocation of randomised group		
		Surgical (*n*=__)	Non-surgical (*n*=__)	Mean difference (95%CI)
PRWE				
DASH				
ED-5D-5D, mean (SD)	EQ-UI			
	EQ-VAS			

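### The stated imputation model for 12-month PRWE does not include randomised group, so an imputed primary result can be biased in either direction

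*SAP article*

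**What the plan says.** Under Methods for handling missing data, imputation has a trigger: "If greater than 10% of the primary outcome data is missing from the randomised sample". Above it, missing 12-month PRWE is "imputed using multiple imputations based on baseline data including age, gender and fracture type as well as PRWE score at 3 months". The same section adds: "A completed case analysis will be performed as a sensitivity analysis". When imputation is triggered, the imputed analysis is therefore primary and the complete-case analysis is secondary to it.

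The analysis that this feeds is described under Primary analysis: "The MD in PRWE scores between the surgical and non-surgical groups will be tested using a two-sample *t* test".

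Under Power and sample size: "We aim to recruit 160 patients to allow for 20% loss to follow-up". Two earlier trials are cited there with losses of 19%.

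Under Sensitivity analyses, "a completed case analysis of the primary and secondary outcomes at 12 months will be performed and compared with the analysis using imputed data", with a qualifier that limits the comparison to the case where imputation was needed.

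Two other sections matter. Data collection describes the baseline data as age, gender, fracture type, radiographic features, healing risk factors and treatment preference; allocation is not on that list. Randomisation and allocation gives the analysts a masked two-group label.

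**The concern.** An imputation model should contain every variable in the analysis that it serves. Here the analysis has one explanatory variable, randomised group, and the stated model leaves it out. Two participants with the same covariates and the same 3-month PRWE would have their missing 12-month scores drawn from the same distribution, whichever treatment they were allocated. Any part of the 12-month treatment effect that does not pass through the 3-month score is then lost among the imputed values. Any part of a 3-month effect that has worn off by 12 months is partly put back.

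What is at stake is the primary estimate, which the plan reads against a threshold of more than 14 points. A shift of 1 to 3 points can decide on which side of that line the result falls.

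**Working it through.** **Inputs from the SAP article.** 64 per group for 90% power at 14 points; two-sided 5% level; 20% loss allowed for; 164 randomised, taken as 82 per arm.

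**The plan's own figures.** 128 / (1 − 0.20) = 160, which matches. The article gives no SD for PRWE, so it was back-solved from "A total of 128 patients (64 in each group) will provide 90% power to detect a difference of 14 points on the PRWE scale": SD = 14 × √(64/2) / (1.960 + 1.282) = 24.4 by the normal approximation, or 24.2 by the t test. SD 24 is used below.

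**Assumptions, not in the document.** SD 24 in both arms at both times; within-arm correlation r between 3- and 12-month PRWE, mainly 0.6; missingness completely at random and equal in the arms; baseline covariates that carry no treatment effect.

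**Formula.** Let D3 and D12 be the true differences at 3 and 12 months and m the fraction missing. With group left out, observed participants contribute D12 and imputed ones contribute b × D3, so

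expected estimate = (1 − m) × D12 + m × b × D3,

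where b is the pooled slope of 12-month on 3-month PRWE:

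b = (r × SD² + D3 × D12/4) / (SD² + D3²/4).

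**Results for m = 0.20, r = 0.6** (SD² = 576, r × SD² = 345.6):

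| D12 | D3 | b | Expected estimate |
|---|---|---|---|
| 14 | 0, or 3-month score also missing | no contribution | 0.8 × 14 = 11.2 |
| 14 | 7 | 370.1/588.25 = 0.629 | 11.2 + 0.88 = 12.1 |
| 14 | 14 | 394.6/625 = 0.631 | 11.2 + 1.77 = 13.0 |
| 14 | 20 | 415.6/676 = 0.615 | 11.2 + 2.46 = 13.7 |
| 14 | 28 | 443.6/772 = 0.575 | 11.2 + 3.22 = 14.4 |
| 5 | 14 | 363.1/625 = 0.581 | 4.0 + 1.63 = 5.6 |
| 5 | 20 | 370.6/676 = 0.548 | 4.0 + 2.19 = 6.2 |

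**Direction.** The estimate falls short when D12 > b × D3, which with equal SDs reduces to D12 > r × D3. It overshoots when D12 is smaller. At D12 = 14 and r = 0.6 the balance point is D3 = 14/0.6 = 23.3.

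**Range.** For D12 = 14, m = 0.20 and r from 0.4 to 0.7, the estimate runs from 12.4 to 13.2 at D3 = 14 and from 13.6 to 14.8 at D3 = 28. With 10% missing and r = 0.6 it is 12.6, 13.5 and 14.2 for D3 = 0, 14 and 28.

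**Simulation check.** 1,500 trials, 82 per arm, 20 imputations, Rubin's rules, r = 0.6, 20% missing. With group omitted, a true 14 gave mean estimates of 11.1, 12.0, 13.1 and 13.6 for D3 = 0, 7, 14 and 20, and a true 5 gave 5.55 and 6.14 for D3 = 14 and 20. With group included, the means were 14.0 for a true 14, and 4.9 and 5.2 for a true 5. Power at D3 = 0 was 0.80 with group omitted and 0.93 with it included; at D3 = 14 it was 0.93 either way.

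**Secondary outcomes.** The missing-data section imputes missing primary outcome data only. The sensitivity section and its Table 11 set complete-case results against imputed results for primary and secondary outcomes. For the secondary outcomes, no imputed analysis is defined.

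**The case against.** The strongest reply has four parts.

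- **The article does not say that treatment is excluded.** The list of baseline variables is open-ended, and the article condenses a signed version 11 of the SAP that is not shown. This stands as a caution: the full plan may name the group. It does not remove the point. The open list extends baseline data, which the article describes without allocation, and the article chose to specify the model. A programmer following it would leave group out.
- **A reader might infer that imputation always pulls the arms together.** The document does not support that. The 3-month PRWE is a post-randomisation outcome that carries some of the treatment effect, so the missing values are not drawn from one undifferentiated pool, and the direction depends on how the effect changes over time.
- **The planned complete-case comparison would reveal the problem.** In part it would: under the conditions assumed here, complete cases centre on the true difference. But the imputed result would remain primary, and a gap of about 1 point could easily be put down to chance or to the missing data themselves.
- **The trigger may never be reached.** The 20% is an allowance, not a forecast, and the plan describes efforts to limit attrition. This stands; the concern is conditional on more than 10% being missing.

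A reader might also infer that the plan errs by having no imputed comparison at or below 10%. The sensitivity section makes that comparison conditional on imputation being needed, so this is a pre-specified threshold, not a contradiction. Imputing at any level of missingness, adding predictors, or adding a tipping-point analysis would be matters of preference.

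**Conclusion.** The point holds in conditional form. The imputation model as stated does not include randomised group and so does not match the t test that it feeds. If more than 10% of 12-month PRWE is missing, which the 20% allowance makes plausible, the primary mean difference can be biased.

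For a true 14 points and 20% missing, the scenarios tried run from 2.8 points too low to about 0.8 too high. The high end needs a 3-month effect of 28 and a correlation of 0.7. With equal effects of 14 at both times and a correlation of 0.6, the loss is about 1 point and simulated power does not change. These sizes rest on an assumed SD, correlation, 3-month effect and missingness pattern, because the article gives none of them. A fixed direction cannot be claimed.

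The mismatch over secondary outcomes is real but minor, and does not touch the primary result.

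**What to change.** In Methods for handling missing data, state that the imputation model includes randomised group, entered as the masked A/B label, or that imputation is run separately within each masked group. The label is already available to the blinded analysts, so masking is unaffected. If version 11 of the SAP already says this, it is enough to confirm it.

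Then reconcile the two sections on secondary outcomes: either define imputation for the 12-month secondary outcomes, or limit the comparison of complete-case with imputed results to the primary outcome and adjust Table 11 to match.

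The cost is a sentence or two of SAP wording and a small change to the code, with no new data. The change should be made and dated before the allocation is unmasked.

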### Randomisation and allocation

Randomisation occurred immediately after consent was gained by the recruiting orthopaedic team, within 1 week of the date of the injury. The orthopaedic team member contacted a central computer-based randomisation service by telephone. Participants were randomised using the method of minimisation. Randomisation was stratified by site, and minimisation, adjusting for gender and age (60–74 years and > 74 years), was employed as recommended by the National Health and Medical Research Centre (NHMRC) Clinical Trials Centre which provided the randomisation service.

Given the nature of the comparisons (surgery versus no surgery), it was not possible to blind the surgeon (study) investigators or participants. While this increases the risk of performance and detection bias, every effort was made to ensure that treatment, other than the interventions under study was otherwise identical in both groups. The primary outcome (PRWE score at 12 months) was collected from participants by blinded researchers, by telephone.

The statistician and the investigators conducting the analysis will remain blinded to the treatment groups. The dataset will be de-identified and treatment allocation will be masked using dummy group names (for example, Group A and Group B). De-identification and masking will be performed by an independent investigator who is not associated with the analysis. Masking of treatment allocation will be maintained until the statistical analysis and interpretation has been completed and two versions of the manuscript have been prepared and agreed to by all authors.

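### The predictors named for imputing 12-month PRWE do not include randomised group; followed as written, this biases the primary treatment difference, usually toward zero

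*SAP article*

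**What the plan says.** Under *Methods for handling missing data*, the trigger is "If greater than 10% of the primary outcome data is missing from the randomised sample". Above it, the missing scores are to be "imputed using multiple imputations based on baseline data including age, gender and fracture type as well as PRWE score at 3 months". The same section adds: "A completed case analysis will be performed as a sensitivity analysis". Once the trigger is met, the imputed data therefore carry the primary result.

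*Data collection* says what counts as baseline data: age, gender, fracture type, radiographic features, healing risk factors and treatment preference. Allocation is not in that list.

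*Primary analysis* compares mean 12-month PRWE between the surgical and non-surgical randomised groups by an unadjusted two-sample t test under intention to treat. *Study hypotheses* treats a difference above 14 points as clinically important.

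On likely missingness, *Power and sample size* says: "We aim to recruit 160 patients to allow for 20% loss to follow-up". It also says that two previous trials "reported loss-to-follow-up rates of 19" per cent.

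**The concern.** An imputation model should contain at least the variables of the analysis that follows it. Here that analysis has only two, PRWE and randomised group, and the group is not named. A model without it assumes that two people with the same baseline data and the same 3-month score have the same expected 12-month score, whichever treatment they were allocated. Any 12-month effect not already visible at 3 months is removed from the imputed scores. For a participant who also lacks the 3-month score, the imputed values contain essentially no treatment difference, because randomisation balances the baseline predictors between arms.

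The allowed loss of 20% is twice the trigger, so on the plan's own planning figure the estimate affected is the primary one.

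**Working it through.** **Inputs from the SAP article.** 164 randomised (taken as 82 per arm); 20% allowance for loss; 10% trigger; difference of 14 points; "A total of 128 patients (64 in each group) will provide 90% power to detect a difference of 14 points on the PRWE scale"; "Comparisons between treatment groups will be tested at the two-sided, 5% significance level".

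**Assumptions, not in the article.** The same SD at 3 and 12 months; within-arm 3-to-12-month correlation ρ of 0.5 or 0.7; 3-month differences d3 from 0 to 28; scores missing completely at random; baseline predictors balanced between arms. Differences are in points favouring surgery.

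**The plan's own figure.** 128/(1 − 0.20) = 160, which reproduces. No SD is stated. Solving the stated power for it gives, by the normal approximation, 14/[(1.960 + 1.282)·√(2/64)] = 24.4, and by the noncentral t, 24.2. I use 24.2 (SD² = 585.6).

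**Trigger.** 10% of 164 is 16.4, so 17 missing scores start imputation. A 20% loss is about 33.

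**Expected estimate without group.** Let f be the fraction missing and d12 the true 12-month difference. Observed participants contribute d12. Imputed ones contribute b·d3, where b is the slope of 12-month on 3-month PRWE with the arms pooled:

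- b = (ρ·SD² + d3·d12/4)/(SD² + d3²/4)
- expected difference = (1 − f)·d12 + f·b·d3

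Worked case, f = 0.20, d12 = d3 = 14, ρ = 0.5: b = (292.8 + 49)/(585.6 + 49) = 0.54, and 0.8·14 + 0.2·0.54·14 = 11.2 + 1.5 = 12.7.

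At f = 0.20 and d12 = 14:

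| d3 | ρ | b | Expected difference | Bias |
|---|---|---|---|---|
| 0 | any | – | 11.2 | −20% |
| 7 | 0.5 | 0.53 | 11.9 | −15% |
| 14 | 0.5 | 0.54 | 12.7 | −9% |
| 14 | 0.7 | 0.72 | 13.2 | −5.5% |
| 28 | 0.5 | 0.50 | 14.0 | none |
| 28 | 0.7 | 0.65 | 14.8 | +6% |

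If everyone lost also lacks the 3-month score, the second term is zero and the result is 0.8·14 = 11.2 whatever d3 is. If half of them lack it (d3 = 14, ρ = 0.5), the result lies midway: (11.2 + 12.7)/2, about 12.0. At f = 0.10 the largest attenuation is 10% (12.6); with d3 = 14 and ρ = 0.5 it is about 5% (13.35).

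With an early benefit only (d3 = 14, d12 = 0, ρ = 0.5), b = 292.8/634.6 = 0.46, and a spurious 0.2·0.46·14 = 1.3 points appears.

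**Simulation check.** 82 per arm, 20% missing, 20 imputations, Rubin's rules, 1,000 runs per scenario, true difference 14. The imputation model held the 3-month score, with and without group.

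| Scenario | Mean difference (power), no group | Mean difference (power), with group |
|---|---|---|
| d3 = 0, ρ = 0.5 | 11.1 (0.79) | 14.0 (0.91) |
| d3 = 7, ρ = 0.5 | 11.9 (0.87) | 14.0 (0.92) |
| d3 = 14, ρ = 0.5 | 12.7 (0.90) | 14.0 (0.92) |
| d3 = 14, ρ = 0.7 | 13.4 (0.94) | 14.2 (0.95) |
| no 3-month score in the model | 11.1 (0.80) | 13.9 (0.90) |

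The simulation agrees with the formula to within about 0.15 points.

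**The case against.** Several points on the other side have force.

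**Silence is not exclusion.** A reader might infer that the plan deliberately leaves the group out. The text does not say so: it introduces its list with the word including, and the article rests on version 11 of the SAP, which is not shown. What stands is that the group is not named. The open list does not repair this, because it is open only to further baseline data, which the article itemises without allocation. Nor did the article leave the predictors to the full plan: it listed them, down to the one post-baseline score.

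**Direction.** A reader might infer that the treatment difference is always pulled toward zero. It is not: a 3-month difference of 28 gives no bias or a 6% overestimate, and an early-only benefit creates a difference where none exists. The plan also hypothesises a clinically important benefit at 3 months, so the 20% attenuation is the extreme case. This limits the size claimed. It does not defend the model, since the 12-month estimate would still depend on the size of a secondary 3-month effect.

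**Likelihood.** The 20% is a recruitment allowance, not observed loss. The need to impute is to be settled at blind review, and the plan takes steps to limit loss. Imputation is foreseeable, not certain.

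**The complete-case comparison.** Under the missingness simulated here, that analysis is unbiased, so a discrepancy would show. It remains a sensitivity analysis and does not correct the primary estimate.

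**The 14-point threshold.** With a true difference of exactly 14, even an unbiased estimate falls below 14 about half the time. One cannot say that the imputation model alone would make the trial miss an important effect; the harm is a biased estimate.

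**Site.** Because "Randomisation was stratified by site, and minimisation, adjusting for gender and age", a reader might infer that site must be added. The primary t test does not adjust for site, so the imputation need not. With 19 sites, 164/19/2 is about 4.3 participants per site and arm, or about 3.5 observed after 20% loss, which is too few for fixed site effects within arm.

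**Conclusion.** The concern holds in this form: the stated predictors omit the variable that defines the primary contrast, and following the sentence literally gives a biased primary estimate whenever 3-month PRWE does not fully carry the 12-month effect.

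In the central case (20% missing, true difference 14, equal 3-month difference, all 3-month scores present) the loss is about 0.8 to 1.3 points. It reaches 2.8 points if the 3-month score carries no treatment difference or is absent for all those lost. Power suffers less consistently: 0.79 to 0.94 without group against 0.90 to 0.95 with it in the scenarios tabulated.

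These sizes rest on an SD inferred from the stated power, on assumed correlations and 3-month differences, on equal arms and on data missing completely at random. The mechanism does not depend on the particular values. The sentence is wrong as written and cheap to improve.

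**What to change.** Replace the list of predictors in *Methods for handling missing data* with a complete one, for example: *Missing 12-month PRWE will be multiply imputed with randomised group (masked Group A/B code) in the imputation model, or separately by randomised group, using age, gender, fracture type and 3-month PRWE as predictors. Missing 3-month PRWE will be imputed in the same chained model.* Choose one of the two options before the data are analysed.

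Site need not be added and should not enter as fixed effects within arm.

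The cost is one sentence and one more variable in the imputation code. No data collection is needed. Analyst masking is unaffected, because *Randomisation and allocation* already provides dummy group names. If version 11 of the SAP already includes the group, only the published sentence needs correcting.
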